## Abstract

**Background:**

Phacoemulsification is one of the most frequent surgeries in the world. However, prolonged use of phacoemulsification machines produces reactive oxygen species which will damage corneal endothelial cells. Ascorbic acid has an antioxidant capacity to neutralize oxidative stress in the anterior chamber. This study will investigate the protective effect of ascorbic acid on corneal endothelial cells in patients with hard nuclear cataracts.

**Methods:**

This study is a double-blinded randomized controlled trial. Samples will be divided into three groups, and 500 mg vitamin C three times daily (1500 mg/day), or placebo will be received for seven weeks. Clinical characteristics, ascorbic acid, malondialdehyde, and total antioxidant capacity of patients in serum and aqueous humor will be measured before and after intervention and phacoemulsification.

**Conclusions:**

Data from this study will reveal the protective effect of oral vitamin C supplementation on the corneal endothelial cells in patients with hard nucleus cataracts.

This trial has been registered at
ClinicalTrials.gov (identifier: NCT06781970; registered on 17 January 2025). The trial record is available at:
https://clinicaltrials.gov/ct2/show/NCT06781970

## Introduction

Cataract is the most probable cause of blindness in Indonesia. Universally, WHO estimated that 51% of blindness in the world is caused by cataracts and there are 20 million people who are blind from cataracts. In 2020, the prevalence of blindness in Indonesia is 1.4% with 81.2%, or three million, being from cataracts. This number progressively increases as aging is the risk factor for cataracts and is positively correlated to cataract density. With 10% of the total population in Indonesia being of geriatric population in 2021, it is predicted there will be more than 50 million elders in Indonesia in 2045 suffering from cataracts.
^
1
^
^,^
^
2
^

Phacoemulsification is the most used cataract extraction method, with a high success rate of 80.1% compared to extracapsular cataract extraction (ECCE) and intracapsular cataract extraction (ICCE).
^
3
^ Phacoemulsification utilizes ultrasonic waves, up to 20,000 Hz, to break apart and emulsify the lens. Mechanic vibration of the probe causes bubbles through the acoustic cavitation phenomenon in the aqueous humor. These bubbles, if popped, will dissociate water molecules and produce reactive free radicals.
^
3
^ Phacoemulsification is safer and more effective than other cataract extraction methods. However, higher power and longer duration of ultrasonic waves from the phacoemulsification probe may cause postoperative complications through the increased number of free radicals.
^
4
^

Free radicals bind with antioxidants in tissues. The imbalance between the number of free radicals and antioxidants in the tissue causes oxidative stress.
^
5
^ On a molecular level, oxidative stress can be measured through various markers, one of which is malondialdehyde (MDA). MDA is the end-product of phospholipid oxidation, in which the phospholipid bond is one of the main targets of reactive oxygen species.

Corneal endothelial cells (CEC) have little to no regeneration capacity, hence CEC damage is irreversible. Naturally, corneal endothelial cells diminish 0.3-0.6% yearly.
^
6
^ This phenomenon is aggravated by increased levels of oxidative stress. Phacoemulsification causes a 40% increase in intraocular free radicals if not followed by sufficient antioxidants. Patients with hard nucleus cataracts undergo a longer duration of phacoemulsification and higher phaco power, hence there is a four times higher risk of endothelial decompensation. Permanent endothelial decompensation is typically observed 4–6 weeks postoperatively, is a condition called bullous keratopathy.
^
7
^ The definitive management of bullous keratopathy is a corneal transplant. However, the ratio of donor availability and demand is 1:70.
^
8
^ There is a need for an alternative solution.

Total antioxidant capacity (TAC) portrays the capacity of a tissue to neutralize oxidants. As much as 73% of TAC in intraocular tissue is ascorbic acid (AA).
^
9
^ The amount of AA and TAC in the aqueous humor is found to be an independent protective factor towards endothelial decompensation. An increase of 1 mM TAC in aqueous humour causes 50 times lowered risk of endothelial decompensation. Protective features of AA towards oxidative stress in the cornea have been proven in vitro and in animal studies. In a rabbit corneal endothelial culture, topical AA is found to lower cell apoptosis.
^
10,
11
^ Using AA in irrigation solution in phacoemulsification for dogs is found to lower endothelial cell density, hexagonality, and variation coefficient.
^
12
^ On mild-to-moderate degree cataract, 500 mg of AA qid. lowers endothelial cell density difference to 30% compared to control.
^
13
^

Vitamin C has been widely studied for its potential to mitigate corneal endothelial damage caused by oxidative stress during phacoemulsification. Previous studies have demonstrated protective effects of vitamin C in mild to moderate cataracts using oral supplementation, as well as beneficial effects of topical administration in experimental animal models.
^
10,
11,
13
^ Oral vitamin C may represent a practical antioxidant due to its wide availability and lower risk of adverse effects compared with other antioxidant strategies such as intravenous vitamin C and intracameral antioxidants. Regarding these findings, we hypothesized that oral vitamin C supplementation increases ascorbic acid levels and overall antioxidant capacity in the aqueous humor and reduces oxidative stress–related endothelial damage during phacoemulsification. However, to date, no clinical studies have specifically evaluated the protective role of oral vitamin c supplementation in patients with hard cataracts undergoing phacoemulsification. On the other hand, aqueous humor will also be replaced by irrigation fluid during phacoemulsification, which may reduce the intraocular antioxidant content. Therefore, oral vitamin C is given postoperatively to restore AA levels in the aqueous humor. Thus, it is expected that the antioxidant effect of AA can suppress postoperative corneal endothelial autophagy and apoptosis, which can cause severe damage to the endothelial layer. Considering that aqueous humor sampling cannot be performed during the postoperative recovery period, it is important to determine whether the levels of MDA, TCA, and AA in the aqueous humor are the same as or correlate with blood levels, as no studies have yet examined these three biomolecular parameters simultaneously in both compartments.

## Protocol

## Methods

### Study design

This is a double-blinded, randomized controlled trial investigating the protective effect of ascorbic acid supplementation on corneal endothelial cells undergoing phacoemulsification. The study will follow the SPIRIT (Standard Protocol Items: Recommendations for Interventional Trials) guidelines.

### Study setting

This study is going to be conducted in the Faculty of Medicine, University of Indonesia with samples from a regional hospital in Cianjur, West Java and Serang, Banten, Indonesia.

### Aims

The aim of this study is to analyze the protective effect of oral ascorbic acid supplementation on corneal endothelial cells which undergo oxidative stress due to phacoemulsification in patients with hard nucleus cataracts. The primary outcome will investigate mean change and percentage in endothelial cell density (ECD) loss prior to and after phacoemulsification, assessed at postoperative follow-up period (day 1, week 1, week 4, and week 6) of patients with hard nucleus cataracts.

The secondary endpoint will investigate mean change in other clinical parameters such as central corneal thickness (CCT), visual acuity, and cells in the anterior chamber during the postoperative follow-up period. This study will investigate differences in MDA levels in aqueous humor, prior to and after phacoemulsification, and compare between groups with vitamin C supplementation and those without. We will also investigate differences in AA, TAC, and MDA levels in serum and aqueous humor at the start of the study and after seven days of supplementation and compare them between the three groups. Furthermore, we will explore the correlation between aqueous humor and serum AA, TAC, and MDA levels.

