### Sample size calculation

A total sampling method was used. The sample size was determined based on the primary outcome of postoperative corneal endothelial cell density (ECD) loss, referring to a previous study by Chee et al.
^
14
^ The minimal sample size calculated for this study was 36 subjects for each group (95% confidence interval, power 80%, β = 0.20, α = 0.05, SD = 201 ​​cell/mm
^2^, expected difference = 132 ​​cell/mm
^2^, subjects should have at least 132 ​​cell/mm
^2^ difference of ECD loss after phacoemulsification in the intervention group). With a 10% additional for anticipating loss to follow-up subjects, the minimal sample size needed was 40 for each group.

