### Statistical analysis

Data from this study will be recorded and analyzed by IBM SPSS 20.0. Sample personal identification, including demographic and clinical characteristics, will be reported in a descriptive analysis. Data distribution of numerical variables will be assessed using the Shapiro–Wilk test with normal distribution will be presented as mean (standard deviation [SD]); non-normal distribution will be reported as median (interquartile range [IQR]). Nominal data will be reported in frequency and percentage. We will use Pearson’s chi-squared test for categorical data. For comparisons among the three groups, one-way ANOVA will be used for normally distributed data, while the Kruskal–Wallis test will be used for non-normally distributed data. Significant group differences will be followed by post-hoc pairwise comparisons using Bonferroni correction for ANOVA or Dunn’s test following the Kruskal–Wallis analysis to account for multiple testing. Pearson’s test will be used to test the correlation between data in aqueous humor and serum. A p-value of less than 0.05 (p < 0.05) will be considered statistically significant.

Effective phacoemulsification time (EPT) and total surgical duration will be included as covariates in the statistical analysis to account for their potential influence on postoperative endothelial outcomes. Multivariable analysis will also be conducted to control for potential confounding variables, including smoking status, occupational exposure, ultraviolet (UV) light exposure, and dietary intake of vitamin C. These variables will be collected through structured questionnaires during the screening.

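### Absolute and percentage ECD loss at four visits are all primary and unranked; if each is tested at 0.05, the chance of a false-positive primary result is roughly 10–25% under assumed between-visit correlations

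*Protocol article*

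**What the plan says.** Protocol article, Aims: "The primary outcome will investigate mean change and percentage in endothelial cell density (ECD) loss prior to and after phacoemulsification". The same sentence then sets the timing at four postoperative visits: day 1, then weeks 1, 4 and 6. Both expressions of loss and all four visits carry primary status, and nothing ranks them.

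Protocol article, Statistical analysis: "For comparisons among the three groups, one-way ANOVA will be used for normally distributed data", with Kruskal–Wallis as the non-normal alternative. The follow-up rule is "Significant group differences will be followed by post-hoc pairwise comparisons using Bonferroni correction for ANOVA or Dunn’s test following the Kruskal–Wallis analysis". The threshold is general: "A p-value of less than 0.05 (p < 0.05) will be considered statistically significant". Effective phacoemulsification time and surgical duration are to be covariates, and a multivariable analysis is planned. No repeated-measures model is named.

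Protocol article, Sample size calculation: "The sample size was determined based on the primary outcome of postoperative corneal endothelial cell density (ECD) loss", with "power 80%, β = 0.20, α = 0.05", SD 201 and "expected difference = 132" cells/mm². This is absolute loss. No visit is attached to it.

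Protocol article, Study status: at submission in September 2025 the study was in the data processing phase.

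**The concern.** One-way ANOVA and Kruskal–Wallis each take one value per patient. Applied to two measures at four visits, they give 2 × 4 = 8 primary three-group tests. The Bonferroni or Dunn step limits error among the three group pairs inside one such test. It does nothing across visits or across the two scales. Covariate adjustment does not reduce the number of tests either.

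Two things are at stake. Any of eight results could be presented as the primary finding, so the 5% error rate is not held for the primary outcome as a whole. And the stated power belongs to one comparison on one scale at a visit the protocol does not identify. With the data already being processed, an unranked list also leaves room for selecting a result after the fact.

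**Working it through.** **1. The plan's own sample size.** Inputs from Sample size calculation: difference 132, SD 201, α = 0.05 (two-sided assumed), power 80%.

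n per group = 2 × [201 × (1.960 + 0.842) / 132]² = 36.4.

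The protocol states 36; rounding up gives 37, a trivial difference. Allowing 10% loss, 36 / 0.9 = 40, as stated. The trial was therefore sized for one two-group comparison at α = 0.05, with nothing set aside for several primary tests.

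**2. Bounds.** If the tests were independent, the family-wise error would be 1 − 0.95^k: 18.5% for k = 4 (one scale, four visits) and 33.7% for k = 8. The tests are strongly correlated, so these are upper limits.

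**3. Simulation under no effect.** Three groups of 36, one-way ANOVA at 0.05 on absolute and percentage loss at four equally correlated visits, 20,000–40,000 trials per setting. The protocol gives no between-visit correlation, baseline ECD or mean loss, so these are assumptions:
- Setting A: baseline mean 2500, SD 250; mean loss 400, SD 201. The two scales correlate at about 0.97.
- Setting B: as A, but baseline SD 350 and mean loss 700. The two scales correlate at about 0.88.

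Chance of at least one significant omnibus test:

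| Between-visit correlation | Absolute loss only, 4 tests (A) | Both scales, 8 tests (A) | Both scales, 8 tests (B) |
|---|---|---|---|
| 0.3 | 17% | 21% | 24% |
| 0.5 | 16% | 19% | 22% |
| 0.7 | 13% | 16% | 18% |
| 0.8 | 12% | 14% | 16% |
| 0.9 | 9% | 11% | 13% |
| 0.95 | 8% | 10% | not run |

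A single test at one visit gave 4.7–5.3%, as it should. Most of the inflation comes from the four visits; the second scale adds about 2 to 6 percentage points.

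**4. Stricter definitions of a false positive.** Same group size, with the correlation between the two scales set directly at 0.90–0.97:
- Significant omnibus test plus a Bonferroni-significant pair, any pair and either direction: about 21% at between-visit correlation 0.3, 11–12% at 0.9, and 8–9% at 0.95.
- The same rule, counting only a false claim that a vitamin C group is better than placebo: about 8% at 0.3, 4% at 0.9 and 3% at 0.95. For one measure at one visit, that rule gives about 1.5%.

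**5. Protecting all eight.** Bonferroni gives 0.05 / 8 = 0.00625 per test. On the protocol's own inputs, n = 2 × [201 × (2.734 + 0.842) / 132]² = 59.3, so 60 per group for 80% power, against 40 planned.

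**The case against.** Several stronger readings are tempting, and the protocol does not support them.

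- **That eight separate tests at 0.05 are stated.** They are not. Testing at each visit is inferred from the only group comparisons named. An analysis plan that is not shown could handle multiplicity differently. This stands as a limit on certainty. It does not remove the point, because the Aims section positively gives primary status to every measure and visit, and a plan that chose one would contradict it.
- **That the error rate is a known figure.** It depends on correlations the protocol does not supply. All four changes share one baseline reading, and the Introduction calls endothelial damage irreversible; both argue for high correlation and so for the lower end of the range. The two scales re-express the same readings, which the simulations already allow for.
- **That the rate is the chance of wrongly declaring vitamin C effective.** It counts any omnibus rejection, including placebo doing better or Group 1 differing from Group 2. For a false benefit over placebo after the planned pairwise step, the figure is about 3–8%.
- **That the power statement matches no identifiable quantity.** The scale is clear, namely absolute loss in cells/mm². Only the visit is missing.
- **That day 1 is uninformative.** Groups 1 and 2 share the same regimen until surgery, so day 1 says little about postoperative supplementation. It can still inform preoperative vitamin C against placebo, and nothing says it is meant to do more.

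**Conclusion.** The point holds. The primary outcome is two scales at four visits without ranking, the named tests use one value per patient at 0.05, and correction stops at group pairs. If each measure is tested at each visit, the chance of at least one false-positive primary omnibus test is roughly 10–25% for assumed between-visit correlations of 0.95 down to 0.3, and about 14–22% for correlations of 0.5 to 0.8. Requiring a Bonferroni-significant pair as well brings the overall range to about 8–21%. No setting examined brings the omnibus rate back to 5%. If one longitudinal test was intended instead, the Statistical analysis section does not say so, and the text needs correcting on that reading too.

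**What to change.** - In Aims, name one primary endpoint: absolute ECD change in cells/mm², the scale of the sample size calculation, from screening to one stated visit. Week 6 is a reasonable choice: it is the last visit and the end of the 4–6 week window in which the Introduction places permanent decompensation. Week 4 also lies in that window, so the reason for the choice should be given.
- Make percentage loss and the other visits secondary.
- In Sample size calculation, state at which visit the 132 cells/mm² and SD 201 were assumed. The protocol does not show that they apply at week 6, so they should not simply be relabelled.
- Date the choice, make it blind to allocation, and report whether that was so. If it cannot be made blind, report all eight results with a multiplicity correction, for example Holm.

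Cost: no new patients or measurements, but more than a change of wording, because a choice made during data processing is credible only if its date and blinding are documented. The sponsor gives up a primary claim based on another visit or on percentage loss. The fallback costs power: Holm's first step is at 0.00625, where the protocol's own inputs would need 60 per group for 80% power.

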### Participants

The target population of this study is patients with hard nucleus cataracts who undergo phacoemulsification. Patients are eligible to be included in this study with the following inclusion criteria: aged above 60 years, have senile cataract in one or both eyes with Lens Opacities Classification System (LOCS) III nuclear opacity grade 4-6 and nuclear color grade 4-6, willing to consume prescription and participate in the study follow up for seven weeks starting from recruitment, and signed the informed consent. Written informed consent was obtained from all participants prior to enrollment in the study.

The exclusion criteria of this study are as follows: patients with vitamin C allergy or sensitivity, undergo intraoperative complications of postoperative infections, have corneal endothelium disorder, history of intraocular surgery, glaucoma, trauma, or other intraocular inflammations, have diabetes mellitus and kidney disorders, or consumes vitamins as daily supplements.

Samples will be dropped out during the study if they did not participate in the study follow-up or consume less than 80% of the prescribed medications.

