### Screening

We screen patients who sign up for a mass cataract surgery event in a regional hospital in Cianjur, West Java, Indonesia. Patients will be asked for information regarding personal identification, history of systemic and ocular diseases, and allergies. They then will undergo ophthalmology examination including uncorrected visual acuity (UCVA) and best corrected visual acuity (BCVA), intraocular pressure using non-contact tonometry (NCT), biomicroscopy slit lamp, and indirect fundoscopy to evaluate anterior and posterior chambers. Lens opacity will then be measured using LOCS III criteria. We will also examine ECD, coefficient of variety (COV), and hexagonality of endothelial cell layers using a specular microscope (REM 4000, Rodenstock, Germany), central corneal thickness (CCT) using Anterior Segment Optical Coherence Tomography (ASOCT), and biometry. Blood samples will be then drawn from patients to measure serum AA, MDA, and TAC.

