### Intervention

Patients will be divided into three groups, each with 40 samples. The first group (n=40) will receive 500 mg oral vitamin C three times daily (1500 mg/day) for one week before surgery to four weeks after surgery. The second group (n=40) will receive 500 mg oral vitamin C three times daily (1500 mg/day) for one week before surgery and a placebo after surgery. The last group (n=40) will receive a placebo one week before surgery to four weeks after surgery. Oral vitamin C 1500 mg/day was chosen based on pharmacokinetic evidence showing that this dosage can achieve stable plasma concentrations and approach a steady-state level during short-term administration.
^
15
^

To minimize potential bias related to surgical variability, all phacoemulsification procedures will be performed using standardized surgical techniques. The surgeries will be conducted by experienced cataract surgeons using the same phacoemulsification machine and standardized operative settings. Key intraoperative parameters, including ultrasound power, irrigation parameters, and the type of ophthalmic viscosurgical device (OVD), will be standardized across all procedures.

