### Post-intervention evaluation

Patients will be asked to come a week after screening. Firstly, they asked the side effects of the supplementation, including gastrointestinal disorders (nausea, diarrhea, epigastric pain). Second blood samples will be then drawn to measure post-intervention serum AA, MDA, and TAC.

Sampling for oxidative stress in the aqueous humour will be performed twice, pre- and post-phacoemulsification. During surgery, after the initial incision, 0.2 mL of aqueous humor will be taken using a 1 cc syringe with a 30 G cannula. Phacoemulsification will then be conducted using standard operating procedure to intraocular lens implantation. Another 0.2 mL of aqueous humor will then be taken three minutes after removing the viscoelastic as a post-phacoemulsification sample. This sampling volume is within the range commonly used in aqueous humor biomarker studies and is considered safe under surgical conditions. Because the sampling will be performed through the surgical incision and the anterior chamber will subsequently be maintained with a balanced salt solution, anterior chamber stability will not be affected.
^
16,
17
^ The pre-phacoemulsification aqueous humour samples will be analysed for ascorbic acid (AA), total antioxidant capacity (TAC), and malondialdehyde (MDA), while the post-phacoemulsification samples will be analysed for MDA levels only. Intraoperative parameters, including effective phacoemulsification time (EPT) and total surgical duration, will be recorded for each procedure. All patients will receive topical medications: levofloxacin 5 mg/mL every three hours for one week, prednisolone acetate 10 mg/mL every three hours for 1 week, and tapered down in 4-6 weeks.

Every patient will be evaluated one day, one week, four weeks, and six weeks post-phacoemulsification to measure study parameters and signs of complications, i.e. inflammation or infection. Patients who experience side effects or complications, including toxic anterior segment syndrome (TASS) or endophthalmitis during the duration of follow-up will be exempted from the study and managed according to the standard operational procedure of the Department of Ophthalmology, Faculty of Medicine, University of Indonesia.

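### The secondary endpoints are mean changes with no named reference point; comparing postoperative values adjusted for screening would remove the ambiguity and, for acuity, probably gain power

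*Protocol article*

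**What the plan says.** In the Aims section the primary outcome has an explicit reference: "endothelial cell density (ECD) loss prior to and after phacoemulsification, assessed at postoperative follow-up period (day 1, week 1, week 4, and week 6"). The next sentence reads: "The secondary endpoint will investigate mean change in other clinical parameters such as central corneal thickness (CCT), visual acuity, and cells in the anterior chamber", and places this in the postoperative follow-up period. No reference value is named for these three measures, and no visit is singled out.

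The Screening section shows that preoperative values exist: "uncorrected visual acuity (UCVA) and best corrected visual acuity (BCVA") are measured, together with CCT and a slit-lamp examination. Eligible eyes have "nuclear opacity grade 4-6 and nuclear color grade 4-6" on LOCS III, and the exclusions include "history of intraocular surgery, glaucoma, trauma, or other intraocular inflammations" (Participants).

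In the Intervention section, the pre- and postoperative vitamin C group is treated "for one week before surgery to four weeks after surgery". The preoperative-only group also starts one week before surgery.

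The Statistical analysis section compares groups by one-way ANOVA or Kruskal-Wallis. The covariates it names are effective phacoemulsification time, surgical duration, smoking, occupational exposure, UV exposure and dietary vitamin C. The screening value of the outcome is not among them.

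**The concern.** A change score needs a stated starting point, and here two are possible.

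- **From screening.** In hard nuclear cataract, preoperative acuity is limited largely by a lens that is removed in every arm. Subtracting it adds variation unrelated to the effect under test. A null result for acuity could then reflect noise rather than lack of effect.
- **Between postoperative visits.** Vitamin C starts before surgery, so the day 1 value is already an outcome. An eye that is better protected on day 1 has less left to recover and shows the smaller change. A real early benefit could disappear or seem to favour placebo.

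These are alternative readings. Both problems cannot apply to the same analysis.

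**Working it through.** **1. The plan's own figure.** The only sample size is for ECD loss (difference 132, SD 201 cells/mm², α 0.05 taken as two-sided, power 80%): n = 2 × (201 × (1.96 + 0.84) / 132)² = 36.4 per group. The stated 36 is reproduced to within rounding, with power 0.796 by the normal approximation; 36 / 0.9 = 40 after 10% loss. There is no corresponding figure for acuity, CCT or cells. Only n = 36 and the standardised effect 132 / 201 = 0.657 are carried forward.

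**2. Change from screening: bias.** Expected arm difference in change = expected difference in the postoperative value − expected difference in the screening value. Screening precedes treatment and arms are randomised, so the last term is zero. The contrast is unbiased, and only precision is at issue.

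**3. Change from screening: precision for acuity.** Let k = preoperative SD / postoperative SD, and r the pre-post correlation.

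- Var(change) / Var(postoperative) = 1 + k² − 2rk, which exceeds 1 whenever r < k/2.
- SD after adjustment for the screening value = postoperative SD × √(1 − r²).

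The documents give no SD, correlation or target difference for acuity. Assumed here: postoperative SD 0.20 logMAR, difference 0.15 logMAR, 36 per arm, one two-sided 5% comparison, noncentral-t power. The unadjusted postoperative value has power 0.881. The adjusted value has 0.881, 0.908 and 0.975 at r = 0, 0.3 and 0.6. For unadjusted change:

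| Preop SD | k/2 | r = 0: SD, power | r = 0.3: SD, power | r = 0.6: SD, power |
|---|---|---|---|---|
| 0.2 | 0.50 | 0.28, 0.602 | 0.24, 0.756 | 0.18, 0.939 |
| 0.3 | 0.75 | 0.36, 0.413 | 0.31, 0.535 | 0.24, 0.741 |
| 0.4 | 1.0 | 0.45, 0.289 | 0.39, 0.363 | 0.32, 0.495 |
| 0.6 | 1.5 | 0.63, 0.168 | 0.57, 0.195 | 0.51, 0.237 |
| 0.8 | 2.0 | 0.82, 0.119 | 0.76, 0.130 | 0.70, 0.146 |

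For preoperative SD 0.4-0.8 and r = 0-0.3, the variance ratio is 3.8 to 17 and power is 12% to 36%, against 88%. With equal SDs and r = 0.6, change beats the unadjusted postoperative value (0.939 against 0.881). Adjustment is at least as good as either in every cell.

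**4. Change from screening: cells and CCT.** Excluding intraocular inflammation implies, as an inference, almost no cells at screening. Change in cells is then close to the postoperative grade, and little is lost. For CCT, no defect of change from screening is shown; adjustment can only help precision.

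**5. Change from day 1 to week 6.** Arm difference in change = week 6 difference − day 1 difference. Simulation: 36 per arm, 20,000 runs, unit SD at each visit, assumed correlation 0.5, so the SD of change is √(1 + 1 − 2 × 0.5) = 1.

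| True benefit, day 1 (SD) | True benefit, week 6 (SD) | Difference in change | Significant for placebo | Significant for vitamin C |
|---|---|---|---|---|
| 0.657 | 0 | 0.66 SD towards placebo | 79% | 0% |
| 0.657 | 0.33 | 0.33 SD towards placebo | 28% | 0.1% |
| 0.657 | 0.657 | none | 2.5% | 2.4% |

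A fading benefit is reversed, and a lasting one is invisible. The algebra is the same for CCT, acuity and cells.

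**The case against.** The strongest reply is that the text most naturally means change from the preoperative value. The secondary endpoint sentence follows directly on the ECD sentence, speaks of other clinical parameters, and so carries the pre-to-post construction forward. Screening measurements of acuity and CCT fit that. No section names a contrast between day 1 and week 6. This stands: a reader might infer that the plan will report a real benefit as harm, but the documents specify no such analysis. They only leave room for it.

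A reader might also infer that the acuity comparison measures the cataract rather than the cornea. That describes the change within each arm. Between randomised arms the cataract component cancels on average, so this inference fails too.

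The power figures rest wholly on assumptions. The 0.15 logMAR difference is 0.75 of the assumed postoperative SD, more than the 0.657 SD used for the primary outcome, and with similar SDs the loss shrinks or vanishes. This also stands, although a wide preoperative spread is plausible across the eligible cataract grades.

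Finally, visit, scale and covariates for secondary endpoints are often left to an analysis plan, and the confounder list is introduced as inclusive rather than closed. That limits the weight of the missing baseline covariate. It does not settle the reference point, because this document itself chose change as the scale. Kruskal-Wallis is already planned for non-normal data, so an ordinal analysis of cells is a small step.

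**Conclusion.** The point holds as a minor one. What is firm is that mean change is fixed as the scale for three secondary measures, without a reference, and that no baseline value is named as a covariate.

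On the more natural reading the contrast is unbiased and the cost is power, mainly for acuity. Under the stated assumptions power falls from 88% to 12-36%; there is no loss if preoperative and postoperative SDs are equal and the correlation is 0.6. On that reading there is no material problem for cells and none shown for CCT.

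On the reading between postoperative visits, an early benefit would be hidden or reversed for all three measures. The size of that effect depends on the assumed pattern of benefit over time.

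It does not follow that the plan is biased, that acuity cannot show an effect, or that the trial's main result is at risk. The primary ECD outcome and its sample size are untouched.

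**What to change.** Replace mean change with comparisons of the postoperative value at stated visits:

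- BCVA in logMAR at week 6, adjusted for screening BCVA.
- CCT at each visit, adjusted for screening CCT.
- Anterior chamber cells as the ordinal grade at each visit, compared by Kruskal-Wallis.

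State that change between postoperative visits is not an efficacy measure. Mean acuity gain can still be reported descriptively.

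The cost is wording and analysis only. BCVA and CCT are taken at screening, and the postoperative visits are already scheduled. The Study status section places the trial in data processing in September 2025, so the definition should be fixed and dated before the group comparisons are run or, if they have been run, reported as a later clarification.
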